#### SHAM stimulation

Device implantation and post-operative optimisation proceeds as above. The habituated sensory threshold is recorded identically. However, the device is then returned to 0 V and (device remains on but will provide no stimulation). At the 6-week time point after device implantation, the patient is re-assessed for sub-optimal efficacy (anticipated in the majority if the fundamental hypothesis is correct) by the un-blinded research delegate or clinician. To maintain blinding, an identical procedure is followed as above; i.e. re-evaluation of sensory threshold and electrode configurations but this is followed by returning the stimulator to 0 V.

#### Procedures for mechanistic studies (subgroup of patients)

Because mechanistic studies involve quite burdensome studies and because anocortical (MEG) studies can only be performed at the Wellcome Trust Laboratory for MEG studies, Aston Brain Centre by highly experienced investigators ([name], [name]), two separate cohorts of patients will be recruited and separately consented for anorectal and anocortical studies. The numbers of patients for each will be defined by ability to recruit and retain patients in these studies and are in part a function of geographical location of recruitment; however, we will aim to recruit 25 patients to the both anorectal and anocortical studies (see ‘Sample size’ section).

##### Anorectal studies

Patients in the London area (several centres) will be identified as potential subjects and provided with the specific PIS. Interested patients will need to make two visits to the GI Physiology Unit at Barts Health NHS Trust. Patients will undergo quick (clinically routine) tests of anal and rectal sensory function. The high resolution manometry catheter (Medical Measurement Systems) is then inserted and a standard (clinically routine and internationally agreed) protocol [28] of basic pressure measurements obtained. Thereafter, the patient will undergo a prolonged recording (total 1.5 h) of anorectal pressures at rest in a semi-recumbent position in a private room before and after a test meal (45 min each phase). During this time, they can watch TV but will be instructed to press an event recorder for any episodes of ‘urge’ or passage of flatus and complete a sensation record. The catheter is then removed and the study is finished.

#### Anocortical studies

Patients in the Midlands area (Sandwell and West Birmingham NHS, University Hospital Birmingham, Heart of England NHS and University of Leicester NHS Trusts) will be identified as potential subjects and provided with the specific PIS. Interested patients will need to make a total of three visits to the Aston Brain Centre.

Only patients known to be proceeding to implantation will be invited for baseline evaluation and this can only proceed after removal of the test electrode (due to magnetic resonance imaging (MRI)) or in those in whom there is good certainty that a tined lead evaluation will progress to implantation. A baseline MEG will be acquired according to the specific protocol developed and tested by the applicants (see Fig. 3). At the same visit (but after the MEG) they will have an MRI head scan. At the second and third visits (SNM or SHAM in random sequence), the patient will have further MEG acquisitions only.

**Fig. 3 Fig3:**
[figure not shown]
Magnetoencephalography (MEG) protocol for anocortical study

### Study visits

The study visits are shown in the Standard Protocol Items: Recommendations for Interventional Trials (SPIRIT) Figure (Fig. 4; Additional file 1).

**Fig. 4 Fig4:**
[figure not shown]
Standard Protocol Items: Recommendations for Interventional Trials (SPIRIT) Figure

#### Visit 0: Screening

Prior to visit 1 patients will be initially assessed for eligibility against the inclusion and exclusion criteria checklist. The multidisciplinary pelvic floor multidisciplinary team (MDT) discussion needs to be reviewed prior to visit 1. Eligible patients will be sent the REC-approved invitation letter and PIS and invited to attend the visit 1 baseline visit. All patients screened will be added to the screening log.

All study visits have a window of ± 1 week for logistical purposes.

### Screening and baseline visits

#### Visit 0: Screening

Prior to visit 1 patients will be initially assessed for eligibility against the inclusion and exclusion criteria checklist. Pelvic floor MDT discussion needs to be reviewed prior to visit 1. Eligible patients will be sent the REC-approved invitation letter and PIS and invited to attend the visit 1 baseline visit. All patients screened will be added to the screening log.

#### Visit 1: Baseline

Eligibility against the inclusion/exclusion criteria will be reviewed, then, after discussing the study and PIS, patients in agreement complete written informed consent. This visit must take place no more than 18 weeks before permanent implantation.

Once a patient has been consented they will have the following assessments:Demographics, standardised medical/surgical history taken including history of incontinence symptoms, gynaecological history and pregnancy test (women of childbearing potential)Clinical examination of perineum, anus and rectum (if not documented previously within 6 months)Baseline outcome assessments: St Mark’s continence score, Deferment time, Longo Score, OAB-Q Short Form, International Consultation on Incontinence Bowel (SF-ICIQ-B) questionnaire, Faecal Incontinence Quality of Life (FI QoL) score and EQ-5D-5 L/Visual Analogue Scale (VAS)

At this visit patients will also be given the 4-week paper bowel diary (which will also record loperamide usage and taught how to use the touch-screen electronic device), which will be started from this visit.

A total of 4 weeks is provided to complete the diary. A viscerosensory bowel diary will also be provided with instructions for completion over 5 days.

### Surgical intervention visits

#### Visit 2a: Test stimulation

A 4-week window must be given between baseline and test stimulation to allow for the completion of the baseline bowel diary. Test stimulation will take place according to routine care, this will require the patient to attend the hospital as an outpatient, and no research data collection is required. Test stimulation is, therefore, not considered a study intervention and will be performed in accord with local clinical practice. Based on previous data [6, 18], 15% of patients will fail temporary SNM evaluation and will not proceed to permanent implantation.

#### Visit 2b: Mechanistic study enrolment

Before permanent device implantation, those participants passing the test stimulation phase or those patients to have tined lead insertion with a high probability of going through to permanent stimulation, will be selected for and consented to the mechanistic study. All patients must have completed the 4-week bowel diary.

Those selected for anocortical studies will then receive the following investigations:MRI headMEG to electrical anal stimulation, anal squeeze, sacral-root suprasensory stimulation, median nerve stimulation

#### Visit 3a: Permanent device implantation (SNM implant)

Following test stimulation patients will be admitted as a day case for permanent device implantation. Eligibility for randomisation will be re-confirmed (assessment baseline diary data). This visit must occur no later than 18 weeks after the baseline visit.

Patients are randomised prior to knife to skin to either one of the two groups:Group 1 will the initially receive sacral neuromodulation andGroup 2 will initially receive SHAM stimulation

Sixteen-week SNM or SHAM periods will be counted from the initial programming not from the day of surgery.

Intraoperative data will be collected including:Lead position – radiological side and foramen level. Number of electrodes in foraminaMotor thresholds for each of the four electrodes on the quadripolar leadPhysiological motor (± sensory) response for the chosen foramen for lead implantationOther intraoperative data: length of op, type of anaesthesia (including use of any paralyzing agent), blood loss, any other complications

#### Visit 3b: Initial programming (T0)

Post-operatively the implant will undergo baseline checks using impedance measurements of the four electrodes to ensure integrity of the electrical system. Patients will have their SNM programmed as per routine care. This can be done in the post-operative recovery period or up to 2 weeks post surgery. All further follow-up visits will be counted from the initial programming not from the day of surgery.

To reduce selection bias, no consenting patient with an implant in situ will be excluded from participation; i.e. regardless of the surgeon’s views on success or otherwise of implantation. At each follow-up visit impedance measurements will be repeated to ensure maintained integrity of the electrical system. If a closed or open circuit is detected (suggesting possible neurostimulator or lead malfunction) then this will be documented. If satisfactory sensory response can be achieved using an alternative electrode configuration then the patient will be reprogrammed and can continue in the study. In the absence of a satisfactory sensory response with an abnormal impedance measurement the patient will still be followed up as per ITT and any changes to treatment will be recorded in the deviation log.

At each visit any change in electrode configuration, sensory threshold and location of maximum bodily sensation will be recorded. The percentage of time the implant has been active for will be recorded and the usage counters reset.

All programming will be performed using the Model 8840 N’Vision clinical programmer. The patient programmer can, therefore, be covered with tamper-proof tape for the entire clinical trial and no access is required to this device apart from to the power on/off button, synchronisation button and implant on/off button.

Following initial programming:Group 1: the sub-sensory amplitude will be recorded along with the electrode configuration used.Group 2: the sub-sensory amplitude will be recorded along with the electrode configuration used before returning the amplitude to 0 V

Any AEs will be collected at this visit and all subsequent face-to-face visits.

### Crossover phases T0 to T32

#### Visit 4: 6-week reprogramming visit (T + 6)

The tamper-proof tape is left on the patient’s programmer, programming is done via the clinician’s programmer.Group 1: patient assessed for sub-optimal efficacy or unwanted effects of stimulation. In the presence of sub-optimal efficacy or adverse effects the electrode configuration can be changed as per reprogramming algorithm. The sensory threshold is once again recorded and device returned to the sub-sensory settingGroup 2: the sensory threshold is recorded and the electrode configuration can be changed if the site of stimulation appears to be sub-optimal (aim for anal stimulation) before returning device to 0 V

#### Visit 5: Assessment (T + 12 to + 16)

All patients will start the 4-week paper bowel diary and 5-day viscerosensory diary. This can be sent by mail or email, a face-to-face visit is not required.

The selected subgroup will have the first of the mechanistic follow-up studies completed (MEG or Anorectal).

#### Visit 6: Crossover visit (T + 16)

At crossover, the device is turned off for 20 min followed by re-evaluation of the sensory threshold and best electrode configuration in the manner outlined above. The intervention is then reversed for each arm.

Paper diary is completed and returned. Follow-up assessment questionnaires (St Mark’s continence score, Deferment time, OAB-Q Short Form, International Consultation on Incontinence Bowel (SF-ICIQ-B) questionnaire, FI QoL score and EQ-5D-5 L/VAS). Patients will also record their satisfaction on a Likert scale.

#### Visit 7: 6-week reprogramming visit (T + 22)

All patients will have a further follow-up 6 weeks after crossover at T22.

Leaving the tamper-proof tape on the patient’s programmer, programming is performed using the clinician’s programmer.Group 1: the sensory threshold is recorded and the electrode configuration can be changed if the site of stimulation appears to be sub-optimal (aim for anal stimulation) before returning device to 0 VGroup 2: patient assessed for sub-optimal efficacy or unwanted effects of stimulation. In the presence of sub-optimal efficacy or adverse effects the electrode configuration can be changed as per reprogramming algorithm. The sensory threshold is once again recorded and the device returned to the sub-sensory setting

#### Visit 8: Assessments (T + 28 to + 32)

All patients will start the 4-week paper bowel diary and 5-day viscerosensory diary. This can be sent by mail or email, a face-to-face visit is not required.

The selected subgroup will have the second of the mechanistic follow-up studies completed, (MEG or Anorectal).

### Open-label cohort follow-up T32–58

#### Visit 9: End of crossover (T + 32)

At 32 weeks (and after collection of final crossover study data), patients will enter the follow-up phase with patient-decisive stimulation (sub- or supra-sensory) as would be normal for routine clinical practice. A member of the clinical team will reprogramme the device accordingly. Further programming and advice can be provided as per routine care during the period 32–58 weeks. All visits or contact with the clinical team during this time will be recorded on the Note to File CRF.

The 4-week paper bowel diary and 5-day viscerosensory diary will be completed and returned at this visit and the set of follow-up assessment questionnaires (St Mark’s continence score, Deferment time, OAB-Q Short Form, International Consultation on Incontinence Bowel (SF-ICIQ-B) questionnaire, FI QoL score and the EuroQol Health Outcome Measure (EQ-5D-5 L)/VAS). Patients will also record their satisfaction on a Likert scale).

#### Visit 10: Final assessment (T + 54 to + 58)

Patients will be asked to complete a further paper bowel diary and 5-day viscerosensory diary for the last 4 weeks (T54–58). During the final visit both the e-diary and paper diaries will be collected. Patients will undergo final reprogramming and complete the outcome questionnaires and Likert scale. Any AEs will be reviewed and resolved. Patients will then be discharged from the study and continue with normal clinical care.

### Concomitant care and interventions

It is inevitable that participants will seek recourse to loperamide and other medications during the course of the programme. Breakthrough loperamide usage is captured on the patient diary and St Mark’s continence questionnaire (see ‘Outcomes’ section). Additional concomitant medication reporting is not required for assessment of eligibility or safety monitoring; e.g. contraindication with the intervention. Thus, concomitant medications will not be recorded.

### Discontinuation criteria (participants and study)

Clinical care will take priority. The intervention plan allows the direct care team to remain autonomous in clinical decisions and modify their approach accordingly. It is unlikely that the intervention will need to be formally discontinued. However, if the direct care team or the research team at any point feel that the intervention is affecting the patient’s recovery, outcome or prognosis then it will be discontinued immediately. The events and circumstances will be recorded. If any safety concerns have arisen, these will be reported according to research governance framework guidelines.

### Withdrawal criteria

Patients can withdraw at any point in the study. The data collected from consent to the point of withdrawal will be kept for the ITT analysis, as outlined in the patient information and consent form.

Patients will be withdrawn from treatment but follow-up data will be continued to be collected if they:Electively withdraw from treatmentAre not fit for surgeryBecome pregnant or intend to become pregnantAre unable to participate due to an concurrent severe illnessDevelop an acute psychological illness causing concerns

Patients will be withdrawn from both treatment and follow-up if they:Choose to withdraw from treatment and follow-up data collectionBecome lost to follow-up (after at least three attempts at contact by research/clinical staff using at least two different methods)Die or become severely incapacitated so follow-up data collection is impossible

### Criteria for early termination

If the DMEC, TSC, REC or sponsor determine it is within the best interests of the participants or trial to terminate the study, written notification will be given to the CI. This may be due to, but not limited to; serious safety concerns, success or failure of the primary outcome, serious breaches, acts of fraud, critical findings or persistent non-compliance that negatively affects patient safety or data integrity. If the study is terminated participants will be returned to the normal follow-up and routine care.

### Outcomes

#### Primary clinical outcome

The reduction in FI events in SNM vs. SHAM phase of crossover (16 and 32 weeks).

Frequency of FI episodes per unit time will be patient-recorded using 4-week paper bowel diaries. While the limitations of this method are well established [29], this remains the ‘gold standard’ in FI [15, 18, 27, 30] (we will, however, be recording for 4 weeks rather than only 2 as in many previous studies). The measure of treatment effect is the average number of FI events per 4-week period for patients undergoing SNM as compared with the average number of events for patients undergoing SHAM simulation. The study is powered to detect a ratio of 0.7. This is not to be confused with the reduction in the actual number of events post intervention for a given patient, where a 50% reduction has frequently been employed, albeit subjectively, to define ‘success’ for that patient [18, 30]. Rather, we use number of events as a quantitative outcome, achieving greater power than a dichotomous outcome of successful/unsuccessful, and we power to detect a 30% reduction, on average, in this outcome on ITT principles.

The paper diary will be completed prior to implantation then at the end of each crossover phase and again at the end of the cohort follow-up.

#### Secondary clinical outcomes

A variety of quality of life questionnaire and bowel diary measures recorded at 16, 32 and 58 weeks:E-event recorder including episodes of faecal material, leakage of flatus, urgency without incontinence, social and physical activity (Fig. 5)Other bowel diary measures: urgency, urge and passive faecal incontinence episodes, use of loperamide and social functioningSummative questionnaire assessments: St Mark’s continence score [31]; OAB-Q SF score, FI QoL score [32]; International Consultation on Incontinence Bowel (SF-ICIQ-B) questionnaire [33]Viscerosensory bowel diary recording quality, site and intensity of defaecatory urgeGeneric QOL: EQ-5D-5 LLikert scale of patient’s global impression of treatment success (scale 0–10) and patient perception of group allocation (blinding success)Electrode settings (including motor, first and habituated sensory thresholds), programming, and, if applicable reprogramming dataAdverse events and morbidity

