#### Randomised, double-blind crossover design overview

Ninety eligible participants will be randomly allocated to two study arms after SNM implantation (see flow diagram below (Fig. 1) and study scheme diagram (Fig. 2)). Both arms have two intervention periods of 16 weeks’ duration (T0–T16 and T16–T32). Efficacy outcomes are derived from assessments in the final 4 weeks of each crossover period (T12–16 and T28–32), thus allowing for almost 3 months’ intervention before outcome assessments. A reprogramming session will be conducted by the routine clinical care team at 6 weeks in both periods of both arms (T6, T22). Time points will have an interval tolerance of ± 1 week for logistical expedience.

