The Model 8840 Clinician programmer is able to access log data of stimulation usage so there is potential to check all data on ON-OFF cycling during the study intervention periods if this is required to validate fidelity of the intervention (a bit like used blister-packs to count unused drugs in a drug trial). During the SHAM period the neurostimulator will be active but not be providing stimulation (current set to 0 V). Therefore, analysis of neurostimulator activity in the SNM and SHAM phases should be equivocal in percentage of neurostimulator ‘use’ and un-blinding one participant would not compromise blinding for the remainder. The digital programming unit (N’Vision Clinician Programmer Model 8840) will not be supplied to the patient but can be used post hoc to determine if the patient has changed settings or switched stimulation on or off during the study (the programmed settings will also have been recorded on a case report form (CRF) by the unblinded clinical team member). The patient will not be removed from the study if the tamper-proof tape has been broken. This will be recorded for statistical analysis.

A nominated member of the research team or normal care clinician will have access to the programmer at the relevant fixed time points for stimulator adjustment (crossover and 6-week reprogramming). This person who will not be blind to intervention status will not otherwise be involved in the research protocol; e.g. outcomes assessments, collection of CRFs, data management.

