The patient will continue with stimulation at sensory threshold for 5 min, and the process then repeated to identify the habituated sensory threshold. Sub-sensory chronic stimulation will then be performed at the level of the habituated sensory threshold [15] setting the device at this level. The maximum stimulation setting will be set at the habituated sensory threshold to ensure that an individual patient is unable to increase the amplitude of stimulation to above the sensory threshold and, therefore, determine whether they are receiving active stimulation or not.

At the 6-week time point after device activation, the patient will be re-assessed by the un-blinded research delegate or clinician. Changes in electrode configuration will be permitted if a patient is having sub-optimal efficacy or significant unwanted effects of stimulation. Any change in electrode configuration or site of sensation will be documented. The habituated sensory threshold will be re-calculated and stimulation thence returned to this level.

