We do, however, accept that the choice of design has some limitations:Although it is acknowledged that a small proportion of patients prefer supra-sensory stimulation (about 10% in our clinical practice), especially in the short term, for double-blinding it is clearly necessary to mandate sub-sensory stimulation and we acknowledge that this is in effect an experimental variant of the therapy used in ‘real life’. We will, however, comply with routine clinical practice by having a reprogramming session at 6 weeks in each arm regardless of intervention status; i.e. in the SHAM arm this will be a ‘pseudo-reprogramming’ event. For the FI indication, a recent randomised observer-blinded comparison showed no difference in effects of supra- and sub-sensory stimulation [27] building on a small study that showed that therapeutic response threshold was significantly lower than sensitivity threshold [36]. However, we acknowledge that some differences in physiological results have been recorded for sub- and supra-sensory stimulation in the patients with slow-transit constipation [37] and this is acknowledged in the study titleWe acknowledge that it is difficult (and labour intensive) to blind patients to SNM in crossover designs, particularly for patients who receive the intervention first and then have it switched to OFF. This proved a problem in a recent study of irritable bowel syndrome [38] in which 75% patients correctly identified that the stimulator was ON or OFF across all crossover phases. This noted, previous crossover studies of FI (accepting limitations in published documentation) have successfully blinded participants. This remains a risk for any placebo-controlled intervention where the number needed to treat is relatively small; i.e. the majority of patients can identify their stimulation status by the effect it has on their symptoms. This noted, the effect size of SNM vs. SHAM remains uncertain (a reason for performing the study)The study does not address the long-term clinical effectiveness, cost-effectiveness and safety of SNM

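### The allocation guess labelled as blinding success is listed only after each efficacy window, so if SNM works an excess of correct guesses cannot by itself show that the blind failed

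*Protocol article*

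**What the plan says.** In the protocol article, Secondary clinical outcomes lists "patient perception of group allocation (blinding success") next to a 0–10 rating of treatment success. The list opens with "A variety of quality of life questionnaire and bowel diary measures recorded at 16, 32 and 58 weeks". The visit texts for weeks 16, 32 and 58 mention questionnaires and a Likert scale but do not name the guess. The texts for initial programming and for the week 6 and 22 reprogramming visits do not name one either.

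On timing, the design overview states: "Efficacy outcomes are derived from assessments in the final 4 weeks of each crossover period (T12–16 and T28–32"). At week 32, "patients will enter the follow-up phase with patient-decisive stimulation (sub- or supra-sensory"), and this phase runs to week 58.

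On what could reveal allocation, the section on the SNM intervention states: "Sub-sensory chronic stimulation will then be performed at the level of the habituated sensory threshold". In the SHAM phase the device is set to 0 V. The limitations in the Discussion describe a general risk for placebo-controlled interventions with a small number needed to treat, namely that "the majority of patients can identify their stimulation status by the effect it has on their symptoms".

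Blinding procedures provides two other sources of data. A broken tamper-proof tape does not remove the patient from the study; instead, "This will be recorded for statistical analysis". The clinician programmer "can be used post hoc to determine if the patient has changed settings or switched stimulation on or off during the study".

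**The concern.** The primary outcome is a diary kept by the patient, so belief about allocation can act on it directly. A measure of blinding should help to separate two routes to a correct guess. On the first, the patient felt stimulation or picked up a cue at a visit. On the second, the patient got better and drew the obvious conclusion. Only the first is a failure of the blind that offers an alternative explanation for the result.

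A guess taken after 16 weeks of treatment and a 4-week symptom diary contains both routes, and no reason for the guess is listed. The ambiguity is greatest when SNM works, which is when readers will ask whether expectation produced the difference. A later analysis plan cannot recover beliefs that were never collected.

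A second risk comes from the Discussion's item on attrition bias. It says that patients who become unblinded would not contribute data, and does not say how unblinding is established. If a late guess were used for this, exclusion would depend on response. That would conflict with the intention-to-treat principle and with the stated analysis of all non-missing data.

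**Working it through.** **Inputs (Sample size section).** Rate ratio 0.7; SD of log(events) 0.775; within-person correlation 0.2; 90% power; 5% significance; 80 participants needed, 90 randomised.

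**Step 1: reproduce the plan's figure.** From the stated ranges, the within-person SD is ln(112/7)/4 = 0.693 and the between-person SD is ln(56/14)/4 = 0.347. The total SD is √(0.693² + 0.347²) = 0.775, and the correlation is 0.347²/0.775² = 0.2. The SD of a within-person difference is 0.775 × √(2 × (1 − 0.2)) = 0.980. Then n = ((1.960 + 1.282) × 0.980 / |ln 0.7|)² = 79.4, which rounds up to 80. With 10% loss, 80/0.9 gives 89, against 90 randomised. The figure reproduces, so 0.980 is the right SD to carry forward.

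**Step 2: correct guesses under a perfect blind.** The protocol gives no model for guessing, so this one is an assumption. The guess follows only the patient's own event counts, with no period or placebo effect, and the 0.2 correlation also holds between baseline and follow-up.

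- Week 32, where the patient names the period with fewer episodes as SNM: Φ(|ln RR| / 0.980). For RR 0.7 this is Φ(0.357/0.980) = 0.642.
- Week 16, where the patient judges change from baseline against a midpoint cut: Φ(|ln RR| / (2 × 0.980)). For RR 0.7 this is 0.572.

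**Step 3: how often a test would signal a broken blind.** This uses an exact two-sided 5% binomial test against 50% with n = 80. The protocol specifies no such test; it serves only as a yardstick.

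| Rate ratio | Week 16 correct | Week 16 signal | Week 32 correct | Week 32 signal |
|---|---|---|---|---|
| 1.0 | 50% | 0.03 | 50% | 0.03 |
| 0.8 | 54.5% | 0.10 | 59.0% | 0.30 |
| 0.7 | 57.2% | 0.20 | 64.2% | 0.67 |
| 0.5 | 63.8% | 0.64 | 76.0% | 0.998 |

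**Step 4: weaker reliance on symptoms.** Suppose half the patients guess from symptoms at week 32 and half guess at random. At RR 0.7 the correct share is (0.642 + 0.5)/2 = 0.571, with a signal about 20% of the time. At RR 0.5 it is (0.760 + 0.5)/2 = 0.630, with a signal about 59% of the time.

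**Step 5: week 58.** The open-label phase runs from week 32 to week 58, which is 26 weeks on a setting that the patient helps to choose and may feel. A belief recorded then does not reflect the blinded periods.

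**The case against.** The strongest reply is that the timing rests on one blanket heading. That heading also covers device settings and adverse events, which are collected at other visits. The visit texts do not name the guess, and the schedule figure is not shown. This stands in part. Whether the guess is repeated at week 58 is uncertain, and an unlisted earlier guess cannot be ruled out. The list is still the only place in the article that gives the measure a time.

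A reader might infer that the measure merely records efficacy and can never show whether the blind held. The documents do not support that. Guesses near 50% would be reassuring. They can be examined by diary response and by the 0–10 rating. Tape breakage and device logs show tampering, though not belief. Sensory thresholds are re-recorded at visits, which bears on whether stimulation could have been felt.

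A reader might also infer that the blind is weak, or that the trial rests mainly on better blinding. Neither follows. Improved blinding is one of seven listed improvements, and the design uses an identical sham reprogramming procedure and disables the patient's amplitude controls. The Discussion's remark about symptoms describes a risk and is followed by a statement that the effect size is uncertain. It does not say that patients will know.

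On the remedy, it is fair to object that the programming visits are run by an unblinded person who is kept out of outcome assessment and CRF collection, and that by weeks 6 and 22 some effect may already be present. Both points shape the fix below.

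**Conclusion.** The point holds in a limited form. The only listed measure of patient belief comes after the efficacy windows, so if SNM works an excess of correct guesses does not by itself show that the blind failed. A week-58 guess, if taken, says nothing useful about the crossover blind.

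At the planned ratio of 0.7, efficacy alone could move correct guesses to about 57% at week 16 and 64% at week 32. These figures rest on the protocol's own variance assumptions and on an assumed model in which guesses follow counts only. They are the upper end for patients who rely on symptoms less than fully. If the effect is nil or small, guesses stay near 50% and the measure remains informative.

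The primary analysis is not affected unless a guess is used to define who counts as unblinded.

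**What to change.** 1. In Secondary clinical outcomes, add the patient's confidence and main reason (felt stimulation, symptom change, something at a visit, no idea) to the week 16 and 32 guesses.
2. Add one early guess in each period with the same items, preferably before the week 6 and week 22 visits. The patient completes it alone and returns it sealed or by post, so that the unblinded programmer does not handle it.
3. Base the assessment of blinding on the early guesses and on the felt-stimulation reason, and report the week 16 and 32 guesses descriptively.
4. State that week 58 is not used as a blinding measure.
5. State that a guess does not make a patient unblinded for the purpose of leaving data out of the analysis, and align the Discussion's item on attrition bias with this.

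The cost is a few extra items, a CRF change and a return envelope or equivalent. Asking early may prompt some patients to speculate. A guess as late as week 6 or 22 may still be partly affected by efficacy, and the early guess in the second period will carry some memory of the first.
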